### Measurements

Upon admission, we measure: arterial blood gases with *P*_a,CO2_, *P*_a,O2_, pH and *St*HCO_3_^−^, firstly to diagnose the AHRF and secondly, in order to titrate the NIV treatment; regular, venous blood samples, analyzing infectious parameters, red and white blood count, kidney- and liver parameters; electrocardiogram (ECG); and a chest x-ray.

These measurements are done as a standard at the acute admission and not as part of the protocol.

At discharge, we measure: lung function, i.e., FEV_1_, FVC and F_I_VC; peripheral oxygen saturation (*S*_pO2%_); arterial blood gases with *P*_a,CO2_, *P*_a,O2_, pH and *St*HCO_3_^−^; height and weight; MRC Dyspnea score; CAT, SRI and ESS questionnaires; and we note status of medication and long-term oxygen treatment (LTOT), when relevant.

For the intervention group, we read ventilator’s SIM card in regard to compliance, daily use, and apnea-hypopnea index (AHI).

At the home visit one week after discharge, we measure: lung function and *S*_pO2%_.

For the intervention group, we ensure that the ventilator, the mask and the hose are well-functioning; and that the patient is well informed and uses the ventilator correctly.

At the outpatient visits, we measure: lung function; *S*_pO2%_; arterial blood gases; weight; exhaled concentration of carbon mono-oxide; MRCD; CAT, SRI and ESS questionnaires; and we note status of medication, smoking, and LTOT, when relevant.

For the intervention group, we read ventilator’s SIM card in regard to compliance, daily use, and AHI.

At each outpatient visit and at the end of the patient’s study period, we collect data on mortality, hospital admissions, exacerbations treated by a general practitioner or an emergency physician, and emergency room visits.

### Collecting of data

All participants have an individual case report file (CRF) in which all data will be noted. The CRF contains nine sections; a front page with the basic information on the participant, i.e., the patient number, date of consent, allocation, ventilator settings (if relevant) etc.; and a section for each event in the study, i.e., admission, discharge, home visit, and the five outpatient visits including completion data in the fifth.

The CRF contains no personally identifiable information. The files are stored in a locked room to which only the investigators have access.

### Data processing

The primary outcome is the difference in time to death *or* AHRF between the LTNIV group and the control group, analyzed as an Intention-To-Treat analysis and calculated in a Cox proportional hazards regression, using Kaplan-Meier and log rank.

The differences between the study’s two groups will be computed using *X*^2^-statistics for the dichotomous variables and t-tests for the continuous variables, assuming that data will follow a normal distribution. Differences in time to a given event are calculated in a Cox proportional hazards regression, using Kaplan-Meier survival statistics and log rank.

For all comparisons, *p* < 0.05 is the level of significance.

For the sample size calculation, we used SAS (Statistical Analysis System, version 9.4).

We will use the latest versions of SAS for the statistical analyses.

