### Randomization

A total of 150 COPD patients will be included from the four wards. The participants are randomized to LTNIV or usual care in a 1:1 ratio, using a computer-generated block-randomization for each center. The participant is presented with a sealed envelope containing a piece of paper with either “A” (= LTNIV) or “B” (= usual care). The randomization list is stored at Gentofte Hospital in a sealed envelope. 50 sealed envelopes are prepared for each center.

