### Sample size/power calculation

Chu et al. showed that the one-year risk of death *or* repeat AHRF for COPD patients having survived an admission with NIV treatment of AHRF is 63.3 % [3]; and, for the LTNIV group in the RCT by Cheung et al., this risk was 38.5 % [6].

We use these risks for the power calculation. We accept a 0.05 risk of type 1 error (α) and 0.2 of type 2 error (β). With a power of 0.8, the needed sample size is 120. With an expected dropout of 20 %, we intend to include 150 participants, 75 in each arm.

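### Randomisation is blocked within each of four centres, but the analyses named include no centre term; stratifying by centre would be a near-free, minor improvement

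*Protocol article*

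**What the plan says.** All references are to the protocol article.

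- **Randomization.** "A total of 150 COPD patients will be included from the four wards". Allocation is 1:1, "using a computer-generated block-randomization for each center". Centre is therefore a stratification factor with four levels. Block size is not given. Fifty envelopes are prepared per centre (200 in all for 150 patients), so recruitment may be unequal across hospitals.
- **Data processing, primary outcome.** Time to death or repeat AHRF is "analyzed as an Intention-To-Treat analysis and calculated in a Cox proportional hazards regression, using Kaplan-Meier and log rank". No stratum or covariate is named, and nothing says that centre is to be left out.
- **Data processing, secondary outcomes.** Dichotomous variables are compared by chi-square and continuous variables by t-test. Other times to event are handled in the same way as the primary outcome. Again no centre term appears.
- **Sample size/power calculation.** With one-year risks of 63.3% and 38.5%, alpha 0.05 and power 0.8, "the needed sample size is 120"; this is raised to 150 for 20% dropout. Centre plays no part in the calculation.

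**The concern.** Blocking within centre makes the two arms nearly balanced in every hospital. If hospitals differ in baseline risk, that balance removes a source of chance variation from the treatment comparison. A test that does not use centre computes its variance as if that variation were still there. The test is then too cautious: its type I error falls below 5% and some power is given away.

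Named without qualification, a log-rank, chi-square or t-test is ordinarily the plain two-sample version. Someone carrying out the section literally would run analyses that leave out the factor by which allocation was organised. At stake is efficiency in a trial whose target power is 80%; there is no risk of a false positive finding.

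**Working it through.** **Inputs from the protocol article.** Control risk 63.3%; LTNIV risk 38.5%; alpha 0.05 (two-sided reproduces the stated size); power 0.80; four centres; 1:1 allocation; one-year follow-up; N = 120 before and 150 after the dropout allowance.

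**Inputs assumed, because the article gives none.** Between-centre SD of the log baseline hazard from 0 to 0.8; four equal centres; blocks of 4; exponential event times.

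**Step 1: reproduce the stated sample size.**
- Hazard ratio implied by exponential times: ln(1 − 0.385) / ln(1 − 0.633) = ln 0.615 / ln 0.367 = 0.485.
- Schoenfeld events: 4 × (1.960 + 0.842)² / (ln 0.485)² ≈ 60.
- Mean event risk: (0.633 + 0.385) / 2 = 0.509. Patients: 60 / 0.509 ≈ 118, close to the stated 120.
- Dropout: 120 / (1 − 0.20) = 150, exact.

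The plan's figures reproduce and do not depend on centre.

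**Step 2: simulate the test with and without centre.** There were 6,000 trials per scenario, censored at one year. The four centres sit at ±0.447 and ±1.342 SD on the log-hazard scale, so the highest-to-lowest hazard ratio between hospitals is exp(2.684 × SD). The base hazard is set so that average control risk stays at 63.3%. The within-centre treatment hazard ratio is 0.485, so average LTNIV risk is not held at exactly 38.5% once SD exceeds 0. Both log-rank versions are applied to the same data, rejecting when |Z| > 1.96.

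| SD of log hazard | Highest : lowest hazard | Power N=120, unstratified v stratified | Power N=150, unstratified v stratified | Type I error, unstratified, N=120 / N=150 |
|---|---|---|---|---|
| 0 | 1.0 | 80.1 v 79.7% | 88.1 v 87.8% | 4.9 / 4.9% |
| 0.2 | 1.7 | 79.0 v 79.3% | 87.6 v 87.8% | 4.9 / 4.6% |
| 0.4 | 2.9 | 77.1 v 79.8% | 85.3 v 87.5% | 4.3 / 3.9% |
| 0.6 | 5.0 | 73.1 v 80.7% | 81.6 v 87.7% | 3.2 / 2.6% |
| 0.8 | 8.6 | 67.0 v 81.6% | 77.5 v 88.3% | 2.1 / 2.1% |

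The Monte Carlo standard error of each power figure is about √(0.8 × 0.2 / 6000) = 0.5 point. Type I error of the stratified test ran from 4.8 to 5.7%. The top value (N=120, SD 0.6) is a little above nominal, so the stratified power in that cell may be slightly flattered.

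**Step 3: read off the difference (stratified minus unstratified).**
- SD 0: −0.4 point at N=120 and −0.3 at N=150, which is the price of stratifying when centres are alike.
- SD 0.2: 0.3 and 0.2 point.
- SD 0.4: 2.7 and 2.2 points.
- SD 0.6: 7.6 and 6.1 points.
- SD 0.8: 14.6 and 10.8 points.

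**Step 4: cross-check.** A separate simulation at N=120 (3,000 trials per scenario, normal centre effects) gave 80.9 v 79.9% at SD 0, 75.5 v 79.1% at SD 0.5 and 71.2 v 79.5% at SD 0.7. The pattern is the same. Its SD 0 result is the source of the cautious upper figure of about 1 point for the cost of stratifying.

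**The case against.** **Silence is not a decision.** A reader might infer that the trial has chosen to ignore centre. The text does not say so: it names methods and is silent on strata. This is a condensed article, and strata are commonly left to the full protocol or SAP, which are not shown. That stands, and for this reason the two sections do not contradict each other. What remains is that the methods as named, most clearly the chi-square and t-tests, have no place for centre in their ordinary form.

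**The power loss is conditional.** A reader might infer that the trial is underpowered on this account. The loss depends entirely on differences between hospitals that the article does not quantify. All four hospitals are in Greater Copenhagen, use the same blood-gas entry criteria and require guideline-optimal treatment, so very large differences are not obviously to be expected. This also stands. An SD of 0.4 already means a 2.9-fold hazard gap between the extreme hospitals.

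**The planned 150 cushions it.** At N=150 the unstratified test still has 81.6% power at SD 0.6. Patients who drop out contribute follow-up until censoring, so the information available plausibly lies between the two columns. This stands too.

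**Validity is intact.** In every scenario the unstratified type I error was 2.1 to 4.9%, so no inflated false positive rate can be claimed.

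**Two tests for one hypothesis.** A reader might also infer that naming both Cox and log-rank leaves real room to choose a p-value. It does not. With a single treatment term and no ties, the log-rank is the score test of the Cox model. In one simulation of 10,000 trials per scenario, not repeated, log-rank and Cox Wald tests fell on opposite sides of 0.05 in 0.6% of trials at N=120, 0.45% at N=150 and 0.17% under the null.

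**Conclusion.** The point holds as a minor, near-free improvement. Allocation is stratified by centre and the analyses named in the article do not use centre. If they are run that way, the primary test is valid but conservative whenever hospitals differ in baseline risk.

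The size rests on an assumed between-centre SD: nothing is lost at 0, under half a point at 0.2, 2 to 3 points at 0.4 and 6 to 8 points at 0.6. Only marked heterogeneity makes it material. The figures also assume equal centres, exponential times and a common hazard ratio across hospitals.

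Confidence is moderate. The design and the named methods are plain in the text, but a fuller plan may already specify stratification, and no power loss is established.

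**What to change.** In Data processing, state that the primary test is the log-rank test stratified by centre, and that the hazard ratio and 95% CI come from a Cox model stratified by centre. For secondary outcomes, state that centre is included: for example, a Cochran-Mantel-Haenszel test or logistic model in place of the plain chi-square, a linear model with centre in place of the t-test, and centre strata for other times to event. If the full protocol or SAP already says this, align the article's wording with it.

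The cost is a few lines of text, with no extra patients or data, since allocation is already organised by centre. If hospitals do not differ, the price is 0.3 to 0.4 point of power in the main simulation and about 1 point in the cross-check. The reported hazard ratio becomes a within-centre one, which should be stated. The change should be fixed before outcome data are compared by arm.

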**Methods:**

Multi-center open label randomized controlled trial of 150 patients having survived an admission with noninvasive ventilatory treatment of acute hypercapnic respiratory failure due chronic obstructive pulmonary disease. The included patients are randomized to usual care or to continuing the acute noninvasive ventilation as a long-term therapy, both with a one-year follow-up period. The primary endpoint is time to death or repeat acute hypercapnic respiratory failure; secondary endpoints are one-year mortality, number of readmissions and repeat acute hypercapnic respiratory failure, exacerbations, dyspnea, quality of life, sleep quality, lung function, and arterial gases.

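### The primary time-to-event comparison names no baseline covariate and no centre stratification, although randomisation is blocked by centre and admission values precede it: a cheap improvement, not an error

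*Protocol article*

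**What the plan says.** The abstract states the endpoint: "The primary endpoint is time to death or repeat acute hypercapnic respiratory failure". Data processing says that it is analysed by intention to treat and "calculated in a Cox proportional hazards regression, using Kaplan-Meier and log rank". No covariate or stratification factor is named, but the section does not say that allocation is the only term in the Cox model.

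Four other parts of the article bear on the point:

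- **Randomization:** allocation is 1:1, with computer-generated blocks separately for each of the four centres.
- **Measurements:** arterial blood gases are taken on admission, "firstly to diagnose the AHRF and secondly, in order to titrate the NIV treatment", together with routine bloods. Lung function, weight, dyspnea score and the questionnaires first appear at discharge.
- **Consent and Design:** the patient is typically informed about two days after admission and is randomised after consenting. Once acute NIV is no longer needed, it is stopped in controls and continued in the LTNIV arm. Discharge comes after that.
- **Collecting of data:** the CRF has a section for the admission.

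**The concern.** Kaplan-Meier curves and the log-rank test in their standard form compare the arms without using baseline information. The natural reading of Data processing is therefore an unadjusted comparison, though the text does not exclude an adjusted one.

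The protocol itself expects patients to differ in risk. Background assumes that earlier AHRF admissions predict new ones and death. Intervention treats patients with a single AHRF episode as a separate group. Discussion makes clear that persistent hypercapnia is not required.

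When risk varies between patients, leaving a prognostic variable out of a Cox model pulls the estimated hazard ratio towards 1 and costs some power, even with perfect randomisation. Chance imbalance between arms of 75 also goes uncorrected. Ignoring centre leaves the analysis out of step with the way patients were allocated.

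The second stake is pre-specification. The trial is open label, and values measured at discharge could easily be mistaken for baseline. Fixing in advance which values may enter the model prevents that.

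**Working it through.** **1. Inputs.** From Sample size/power calculation: control one-year risk 0.633 ("having survived an admission with NIV treatment of AHRF is 63.3" %), LTNIV risk 0.385 ("this risk was 38.5" %), α 0.05, power 0.80, dropout 20 %. Sidedness is not stated; two-sided is assumed.

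**2. The plan's own figure.** The plan states: "With a power of 0.8, the needed sample size is 120". The two-proportion formula with unpooled variance gives, per arm,

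n = (1.960 + 0.842)² × [0.633×0.367 + 0.385×0.615] / (0.633 − 0.385)² = 7.849 × 0.4691 / 0.0615 = 59.9, so 60 per arm and 120 in all.

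With dropout, 120 / (1 − 0.20) = 150. Both figures reproduce, and neither relies on adjustment.

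**3. Power of the unadjusted time-to-event test.** Under proportional hazards, HR = ln(0.615) / ln(0.367) = 0.485, so |ln HR| = 0.724. Mean risk is (0.633 + 0.385)/2 = 0.509. Schoenfeld's approximation is power = Φ(√events × |ln HR| / 2 − 1.96).

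- 120 evaluable: 120 × 0.509 = 61.1 events, power 0.807.
- 150 with no loss: 150 × 0.509 = 76.3 events, power 0.885.

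The unadjusted test meets the 80 % target.

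**4. What adjustment adds.** The documents give no prognostic strength, so it is an assumption and is shown as a range. Trials of 150 patients with 20 % dropout (about 70 events) were simulated, with three continuous baseline covariates entered separately in the Cox model. Strength is the log hazard ratio per SD of the combined score.

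| Assumed log-HR per SD | Unadjusted power | Adjusted power | Change (points) |
|---|---|---|---|
| 0 | 84.5 % | 84.3 % | −0.2 |
| 0.3 (HR 1.35) | 83.9 % | 85.5 % | +1.6 |
| 0.5 (HR 1.65) | 84.3 % | 88.0 % | +3.7 |
| 0.7 (HR 2.0) | 86.2 % | 93.3 % | +7.1 |

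A separate simulation with one covariate and 120 evaluable patients (2000 trials per setting, Monte Carlo error about 1 point) gave a similar pattern: 78 to 79 %, 80 to 82 %, 81 to 85 % and 82 to 91 % at the same four strengths. Centre strata and a binary history covariate were not part of these runs.

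**5. If the true effect is smaller.** Background reports 38.5 % as a yearly rate of repeat AHRF, while the sample size section uses it as the risk of death or repeat AHRF. The effect on the composite could therefore be smaller than planned. With an LTNIV risk of 0.45 (an assumption), 120 evaluable patients and log-HR 0.5 per SD, power goes from 53 % unadjusted to 62 % adjusted.

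**6. Change of target.** With marginal risks held at 0.633 and 0.385, the conditional hazard ratio is 0.454 at log-HR 0.5 per SD, against 0.485 unadjusted.

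**7. Which values qualify.** Admission gases precede consent and hence randomisation, and the CRF has a place for them. Discharge values follow randomisation and may already reflect the different handling of NIV in the two arms. Age is not among the measurements or CRF items that the article names. AHRF history must be known in the LTNIV arm, because the one-month rule in Intervention depends on it. The article does not say that it is recorded for controls.

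**The case against.** The strongest reply is that nothing here is wrong. An intention-to-treat log-rank or Cox comparison without covariates is a valid primary analysis. A condensed article may leave a covariate list to the full protocol or analysis plan. This stands: the silence is not a defect, and the point is worth making only because the section does name its tests and a better version of them costs almost nothing.

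A reader might infer three stronger things, and the documents support none of them:

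- **That the admission gases are known to be prognostic.** No section says so. Background says that little is known about predictors of AHRF; the predictors it cites or assumes are earlier exacerbations and admissions. Eligibility also truncates pH, PaCO2 and StHCO3, which may limit what they explain.
- **That the trial is underpowered, or gives up power it could have for nothing.** It meets its 80 % target unadjusted. The gain depends wholly on an unknown strength, and the adjusted hazard ratio answers a somewhat different, conditional question. Preferring the marginal one is defensible.
- **That a log-rank test cannot use baseline information.** A stratified log-rank test can use categorical factors, centre among them.

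**Conclusion.** The point holds as a recommendation to pre-specify, not as the correction of an error. The primary comparison is described without a covariate and without the factor used to block the randomisation, although suitable pre-randomisation values exist. The benefit is about 0 to 4 points of power for a combined score of no to moderate strength, and about 7 points for a strong one. Almost nothing is lost if the covariates turn out to be uninformative.

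These sizes rest on assumed prognostic strengths, the plan's own risks of 0.633 and 0.385, 20 % dropout, and a simulated model without centre strata. No single figure can be derived from the documents. If the full protocol or analysis plan already specifies adjustment, the point falls away.

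**What to change.** In Data processing, state that the primary test is the allocation term of a Cox model stratified by centre, with these covariates fixed in advance:

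- age;
- admission PaCO2 (or pH, one of the two chosen now);
- first versus repeat AHRF admission, the predictor that Background assumes.

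Before adopting the list, confirm that age and AHRF history are recorded before randomisation in both arms. State that no discharge measurement enters the primary model. Report the unadjusted log-rank test and the Kaplan-Meier curves as supporting analyses.

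The cost is a few sentences and, if needed, two CRF items. The sample size need not change. The reported hazard ratio becomes conditional on the covariates and centre, which should be said when it is interpreted, and there is no gain if the covariates are not prognostic.

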### Aim

The aim of this RCT is to investigate whether LTNIV can reduce mortality or repeat AHRF in patients who have been admitted for NIV treatment of AHRF due to COPD; and, secondarily, whether LTNIV can reduce mortality per se and the number of repeat AHRF, readmissions, and exacerbations, and improve quality of life.

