### Outcomes

Primary outcome is difference in time to death *or* repeat AHRF between the study’s two groups. AHRF is defined as a pH < 7.35 and a *P*_a,CO2_ > 6 kPa despite optimal treatment according to GOLD guidelines, i.e., nebulized bronchodilators and intravenous corticosteroids [2].

The secondary outcomes are differences in the following variables; one-year mortality, admissions due to COPD; admissions due to repeat AHRF; visits to the emergency department or to an emergency physician due to COPD; exacerbations treated with oral corticosteroids or oral antibiotics; body mass index; forced expiratory volume in one second (FEV_1_); cost efficiency; health-related quality-of-life (HRQoL), measured by COPD Assessment Test (CAT) and Severe Respiratory Insufficience Questionnaire (SRI); sleep quality, measured by the Epworth Sleepiness Scale (ESS); apnea/hypopnea index (AHI); and Medical Research Council's Dyspnea scale (MRCD).

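### Secondary event counts have no test of their own, and the chi-square and t-tests offered ignore time at risk, which favours the arm with more deaths

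*Protocol article*

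**What the plan says.** The Aim section asks, as a secondary question, "whether LTNIV can reduce mortality per se and the number of repeat AHRF, readmissions, and exacerbations". The Methods part of the Abstract likewise lists "number of readmissions and repeat acute hypercapnic respiratory failure, exacerbations" among the secondary endpoints. The Outcomes section repeats these variables and adds emergency visits ("admissions due to COPD; admissions due to repeat AHRF; visits to the emergency department or to an emergency physician due to COPD"). It does not say whether each is a count, an any-event indicator or a rate.

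The Data processing section gives three tools for comparing the groups:
- chi-square "statistics for the dichotomous variables";
- "t-tests for the continuous variables, assuming that data will follow a normal distribution";
- for event times, "Differences in time to a given event are calculated in a Cox proportional hazards regression, using Kaplan-Meier survival statistics and log rank".

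It mentions no count model, rate or person-time, and does not say how death is treated when the event of interest is non-fatal.

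**The concern.** A patient can be readmitted only while alive and under observation. Someone who dies in month two contributes few admissions, and a raw count scores that as a good result. If LTNIV prolongs life, as the Discussion expects, its patients have longer to accumulate events. A comparison of raw counts, or of the proportion with any event, then mixes the survival benefit into the event comparison with the wrong sign. A real fall in the event rate could be hidden, or an apparent excess could appear where the rates are equal. These outcomes are named in the trial's aim, so readers would give them weight.

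Dropout, expected at 20%, also shortens time at risk and would add to the distortion if it differed between arms.

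**Working it through.** **The plan's own figure.** No figure is given for the counts. The only one is the sample size for the primary endpoint, and it reproduces. With 63.3% v 38.5%, two-sided 0.05, power 0.80 and unpooled variance: (1.960 + 0.842)² × (0.633×0.367 + 0.385×0.615) / 0.248² = 7.849 × 0.4691 / 0.0615 = 59.9, so 60 per arm and 120 in total; 120/0.8 = 150.

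**Inputs from the Background section.**
- One-year mortality 49.1% (cited cohort of AHRF survivors).
- 20% (4 of 20 patients in the authors' uncontrolled LTNIV series).
- 33% v 12% (cited randomised trial in stable COPD).

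**Assumptions not in the article.** Constant hazards; 2 events per person-year; between-patient gamma variance of the event rate from 0 to 1; an intermediate scenario of 49.1% v 35%.

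**Step 1: time alive.** With one-year mortality m and a constant hazard, mean time alive in the year is m / (−ln(1−m)).

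| Control v LTNIV mortality | Years alive, control | Years alive, LTNIV | Ratio |
|---|---|---|---|
| 49.1% v 20% | 0.491/0.675 = 0.727 | 0.200/0.223 = 0.896 | 1.23 |
| 33% v 12% | 0.330/0.400 = 0.824 | 0.120/0.128 = 0.939 | 1.14 |
| 49.1% v 35% (assumed) | 0.727 | 0.812 | 1.12 |

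With equal event rates while alive, the ratio of mean counts equals the last column. This step needs no assumed event rate.

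**Step 2: what the tests then show.** At 2 events per person-year and 49.1% v 20%, mean counts are 2 × 0.727 = 1.45 and 2 × 0.896 = 1.79. In simulated trials with 75 per arm and no rate difference, the t-test calls LTNIV significantly worse in about 15% (gamma variance 1), 20% (0.5) and 30% (0) of trials. At 33% v 12% the range is about 8-17%, and at 49.1% v 35% about 7-12%. The nominal figure is 2.5%.

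Reducing the count to any event does not help. The chance of at least one event is r/(r+d) × (1 − e^−(r+d)), with event rate r = 2 and death hazard d. This gives 70% for control (d = 0.675) and 80% for LTNIV (d = 0.223). At gamma variance 0, chi-square calls LTNIV worse in 33% of trials, while an events-per-person-year comparison gives a rate ratio of 1.00 and 2.7%.

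**Step 3: a true 25% rate reduction.** The count ratio becomes 0.75 × 1.23 = 0.92 at 49.1% v 20%, and 0.75 × 1.14 = 0.86 at 33% v 12%, so an apparent fall of 8% or 14%. At 49.1% v 20% the t-test favours LTNIV in about 5-8% of trials. Analysis by person-time does so in about 58% (gamma variance 0), or about 25% with a negative binomial model (variance 1).

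**Step 4: times to non-fatal events.** From 63.3% for the composite and 49.1% for death, under constant hazards:
- composite hazard −ln(0.367) = 1.002; death hazard −ln(0.509) = 0.675; AHRF hazard 1.002 − 0.675 = 0.327;
- one minus Kaplan-Meier: 1 − e^−0.327 = 27.9%;
- true cumulative incidence: (0.327/1.002) × 0.633 = 20.7%.

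With the same AHRF hazard and 20% mortality, one minus Kaplan-Meier is again 27.9%. True incidence is (0.327/0.550) × (1 − e^−0.550) = 25.2%. Kaplan-Meier therefore overstates incidence in both arms, more so where more patients die, but shows no difference between arms. A log-rank test censoring at death gave hazard ratios of 1.00-1.01 and false findings against LTNIV in 2.2-2.6% of trials when death and events were independent.

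**The case against.** **No test is assigned to counts.** This is true. A t-test for counts is an inference from the short list of tools. Admissions could be analysed as time to first event, which the list covers, and a fuller analysis plan may hold a rate model. If the point were only missing detail, it would not be a finding against a condensed article. What keeps it is that the Data processing section does say how group differences will be computed, the Aim and Abstract do say number of events, and no listed tool for non-time variables uses time at risk.

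**The mortality contrast is high.** The 20% comes from 20 highly selected, uncontrolled patients set against an external cohort. The 33% v 12% is from a randomised trial, but in stable patients. Hence the range above; with equal mortality the distortion vanishes.

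**The mean count over a year is a legitimate quantity.** It is, for describing hospital use. It cannot be read as the effect of LTNIV on the tendency to be readmitted when survival differs. Reporting mortality alongside warns the reader but does not correct the comparison.

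**The remedy is imperfect.** This also stands. If the same frailty drives death and events (assumed gamma variance 0.5-1.0), the person-time rate ratio was still 1.05-1.24 with no true effect.

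**A stronger reading about Kaplan-Meier.** A reader might infer that the planned Kaplan-Meier and Cox analyses ignore death and so make the longer-surviving arm look worse. The article is silent on death here; it does not say death is ignored. Step 4 shows no such bias under independence. Under the assumed shared frailty the log-rank hazard ratio rose only to 1.03-1.11.

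**Conclusion.** The point holds for the counts. Analysed with the tools listed, the number of readmissions, AHRF episodes, emergency visits and exacerbations would be compared without regard to time at risk, in a trial that expects survival to differ. The distortion is a factor of 1.14 to 1.23 in mean counts at the article's own mortality figures, resting only on constant hazards and equal event rates while alive. The rejection percentages rest further on the assumed 2 events per person-year and the assumed between-patient variance, and should be read as ranges.

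For times to non-fatal events, the remaining fault is descriptive: one minus Kaplan-Meier overstates absolute incidence (27.9% v 20.7%). It is not a bias against the longer-surviving arm.

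Nor should a reader infer that the main result is at risk. The primary endpoint includes death, so it and the sample size are untouched. The change is advisable because these secondary outcomes are named in the aim.

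**What to change.** In the Data processing section:

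1. State that counts of COPD admissions, AHRF admissions, emergency visits and exacerbations are analysed by negative binomial regression with log(time alive and in follow-up) as offset, and that rate ratios are reported beside mortality by arm.
2. State as a limitation that the offset corrects for unequal follow-up but does not remove selection of frail survivors.
3. For time to a non-fatal event, keep the Cox model, reported as a cause-specific hazard ratio, and show cumulative incidence (Aalen-Johansen) with death as a competing event in place of one minus Kaplan-Meier.

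The cost is mainly analysis wording. The Measurements section already provides for data on mortality, admissions, exacerbations and emergency visits at each outpatient visit and at the end of the patient's study period. The article does not say that dates of death, dropout and last contact are recorded; the offset needs them, so their presence in the case report file should be confirmed.
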